## Abstract

**Introduction::**

To investigate the gene rearrangement and mutation of lymphoma biomarkers including (Immunoglobulin H (IgH), Immunoglobulin kappa (IGK), Immunoglobulin lambda (IGL), and TCR) in the lymphoma diagnosis.

**Methods and analysis::**

Paraffin tissue samples from 240 cases diagnosed as suspected lymphoma in the department of pathology, Deyang City People's Hospital from June 2020 to June 2021 will be enrolled. Deoxyribonucleic acid extraction and Polymerase Chain Reaction (PCR) amplification will be performed in these paraffin tissue samples. Immunoglobulin and T cell receptor (TCR) rearrangement will be analyzed by hetero-double chain gel electrophoresis and BioMed-2 standardized immunoglobulin gene rearrangement detection system. In this study protocol IGH gene rearrangement, IGK gene rearrangement, both IGH and IGL gene rearrangement, both IGH and IGK gene rearrangement, both IGK and IGL gene rearrangement, both IGH, IGK and IGL gene rearrangement, TCR gene rearrangement and positive Ig/TCR rearrangement will be analyzed.

**Discussion::**

In this study, we will use B and T cell lymphoma analysis focusing on IgH, IGK, IGL, and TCR gene rearrangement, so as to provide early guidance for the diagnosis of lymphoma. Second generation sequencing technology is helpful in the differential diagnosis of lymphoma.

**Trial registration::**

Chinese Clinical trial registry: ChiCTR2000032366.

## Introduction

1

Hematologic malignancies are divided into 5 categories: Hodgkin lymphoma, non-Hodgkin lymphoma (NHL), myeloma and acute and chronic leukemia.^[1]^ There are many types of NHL, meanwhile, diffuse large b-cell lymphoma (DLBCL) is the most common type in adults.^[2]^ Approximately one third of DLBCL patients cannot be cured by standard immunochemotherapy due to the high heterogeneity and multiple factors (such as age and gender).^[3,4]^ Therefore, different therapeutic approaches are needed, for instance, morphological, genetic, immunophenotypic and clinical tools.^[5]^

Genome rearrangement is an important oncogenic mechanism for human tumors. Detection of immunoglobulin (IG) and T cell receptor (TCR) gene rearrangement may be specific markers for lymphocyte cloning and hence indicators of lymphoma onset.^[6]^ Gene mutation detect is a new and useful approach for diagnosis of malignant lymphocyte cloning when combining histopathology and immunophenotypic analysis.^[7]^ Recently, biomed-2 cloning analysis technology has solved the problem of false positive results caused by traditional Polymerase Chain Reaction (PCR) and has gradually become a recognized standard for PCR-based Ig/TCR cloning detection.^[8–10]^ This study protocol aims to survey the clinical value of gene rearrangement and mutation in lymphoma diagnosis.

## Materials and methods

2

### Main aims

2.1

We aim to clarify the association of gene rearrangement and lymphoma diagnosis.

### Study registration

2.2

The protocol scheme matches PRISMA's reporting standards. This study protocol was registered on Chinese Clinical trial registry (http://www.chictr.org.cn/index.aspx) with an ID of ChiCTR2000032366.

### Participants

2.3

Paraffin tissue samples from 240 cases diagnosed as suspected lymphoma in the department of pathology, Deyang City People's Hospital from June 2020 to June 2021 will be collected.

#### Inclusion criteria

2.3.1

Tissue samples of Patients who are suspected to be lymphoma, regardless of lymphoma types age, sex, inside or outside the lymph nodes, will be included.

#### Exclusion criteria

2.3.2

Basic clinical information of patients is not complete.

The size of paraffin tissue could not meet the test requirements of HE, immunohistochemistry, and gene rearrangement will be excluded.

#### Diagnostic criteria

2.3.3

2008 WHO classification criteria for hematopoietic and lymphoid tumors.

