#### Deoxyribonucleic acid (DNA) extraction and rearrangement detection

2.4.2

Genomic Deoxyribonucleic acid (DNA) will be extracted from 240 paraffin embedding tissue samples. The IGH, Immunoglobulin kappa (IGK), LGL, T cell receptor gamma (TCRG), T cell receptor delta (TCRD), and T cell receptor beta (TCRB) rearrangement in genomic DNA will be analyzed using the European biomed-2 system. Additionally, the Next-generation sequencing (NGS) technology will be adopted for probing mutations. The detected mutations in lymphoma associated genes will be recorded, as well as the mutation ratio (the percentage of reads of this mutant site to the total number of reads that cover this site).

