## Discussion

3

There are 2 categories of lymphoma: Hodgkin lymphomas and NHL.^[11,12]^ NHL can be driven by genetic and environmental risk factors.^[13]^ DLBCL is the most common adult lymphoid malignancies^[14,15]^ which is consistent with our analysis. It is known that DLBCL is more common in adults than in children, with a dramatic increase in incidence at 50 years old.^[16]^ Although some patients can be relieved after treatment, due to the non-specific molecular pathogenesis of DLBCL^[17]^ and its significant heterogeneity, some advanced-stage patients cannot be cured by standard immunochemotherapy.^[12]^ Therefore, early detection and treatment of DLBCL are still a challenging problem. To date, gene analysis combined with histopathology and immunophenotypic analysis can provide a new approach for the diagnosis of malignant tumors.^[18]^ Genomic rearrangement is an important oncogenic mechanism in human tumors,^[19]^ which may produce fusion transcripts encoding chimeric proteins with new functions.^[6]^ Many studies have shown that the IG gene rearrangement is a specific marker of B lymphocyte cloning^[19,20]^ and can be used in diagnosis of B cell lymphoma.^[21,22]^ The detection of IG gene rearrangement can help determine the nature of the lesion and distinguish between benign or malignant lymphocytes.^[23,24]^ Additionally, TCR rearrangement is another criterion for the diagnosis of lymphocyte disease.^[10,25]^ Based on the PCR of IG and TCR, it has been standardized in the suspicious lymph node hyperplasia.^[26,27]^ However, early PCR strategy always induce false negatives and false positives, and it is unable to accurately distinguish between monoclonal and polyclonal PCR products.^[28,29]^ When taking the advantages of standardized BioMed-2, the disadvantages of traditional PCR assay can be addressed,^[8,30]^ and this multiple detection showed a great clinical value for PCR based Ig/TCR cloning detection.^[31]^

In conclusion, standardization of BioMed-2 gene rearrangement detection system is a powerful tool of lymphoma diagnosis, IGH, IGK, Immunoglobulin lambda (IGL) and TCR gene rearrangement distributions are distinct in different subtypes of lymphoma.

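### The reference diagnosis in section 2.3.3 is not kept independent of the Ig/TCR and NGS results, so the association it is meant to test can be biased upward

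*Protocol article*

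**What the plan says.** The protocol article states its aim in section 2.1: "We aim to clarify the association of gene rearrangement and lymphoma diagnosis". The Introduction puts it in terms of use: "This study protocol aims to survey the clinical value of gene rearrangement and mutation in lymphoma diagnosis".

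The diagnosis side of that comparison is defined in section 2.3.3, whose entire content is "2008 WHO classification criteria for hematopoietic and lymphoid tumors". The section does not say which findings feed the diagnosis, or whether the molecular results are available to whoever makes it.

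The test side is in section 2.4.2: Ig and TCR "rearrangement in genomic DNA will be analyzed using the European biomed-2 system", with NGS added for mutations. Section 2.3.2 requires enough tissue for all three procedures: "The size of paraffin tissue could not meet the test requirements of HE, immunohistochemistry, and gene rearrangement will be excluded". Sections 2.4.1 and 2.4.2 describe HE with immunohistochemistry and the molecular work under separate headings, but state no order and no separation of results.

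The Discussion describes the molecular result as diagnostic: "TCR rearrangement is another criterion for the diagnosis of lymphocyte disease", and "gene analysis combined with histopathology and immunophenotypic analysis can provide a new approach for the diagnosis of malignant tumors". The Introduction likewise presents mutation detection as useful for diagnosis in combination with histopathology and immunophenotype.

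**The concern.** A study of a test's diagnostic value needs a reference diagnosis that does not depend on the test. The cases here are suspected lymphomas, the setting in which a clonality result would be consulted. A pathologist following the article could properly use that result to decide a case that morphology and immunohistochemistry leave open. The case would then count as agreement between rearrangement and diagnosis, whatever the truth.

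The open cases are also where the test could add most to existing methods, so the main question would be answered least reliably where the answer matters most. A larger sample does not remove this kind of bias. Nor can it be repaired at analysis if no diagnosis was recorded before the molecular result was seen.

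**Working it through.** **No figure to reproduce.** The article gives 240 samples but no prevalence, accuracy, share of open cases or target precision. Apart from the total of 240, every input below is an assumption, used only to show direction and order of size.

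**Direction.** Suppose the reference is correct outside the open cases and follows the test inside them.

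- Apparent sensitivity = (true positives among settled cases + all open test-positives) / (settled lymphomas + all open test-positives).
- Against the true value, open false negatives leave the denominator, and open false positives join both numerator and denominator. Neither step can lower the ratio.
- The same holds for specificity. The bias is therefore never downward, and it is zero when no case is decided by the test.

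**Illustration 1.** Assume 160 lymphomas and 80 non-lymphomas, true sensitivity 80%, true specificity 90%, and E open cases split evenly and settled by the test. For E = 24 (10% of 240):

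- Settled cases: 160 − 12 = 148 lymphomas and 80 − 12 = 68 others.
- Open test-positives: 12 × 0.8 + 12 × 0.1 = 10.8. Open test-negatives: 12 × 0.2 + 12 × 0.9 = 13.2.
- Apparent sensitivity: (148 × 0.8 + 10.8) / (148 + 10.8) = 129.2 / 158.8 = 81.4%.
- Apparent specificity: (68 × 0.9 + 13.2) / (68 + 13.2) = 74.4 / 81.2 = 91.6%.
- Odds ratio: (129.2 × 74.4) / (29.6 × 6.8) = 47.8, against a true (128 × 72) / (32 × 8) = 36.

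| Open cases | Apparent sensitivity | Apparent specificity | Odds ratio |
|---|---|---|---|
| 0 | 80.0% | 90.0% | 36 |
| 24 (10%) | 81.4% | 91.6% | 47.8 |
| 48 (20%) | 130.4/157.6 = 82.7% | 76.8/82.4 = 93.2% | (130.4 × 76.8)/(27.2 × 5.6) = 65.7 |
| 72 (30%) | 131.6/156.4 = 84.1% | 79.2/83.6 = 94.7% | (131.6 × 79.2)/(24.8 × 4.4) = 95.5 |

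**Illustration 2.** Now let a share u of all cases be decided by the test, whatever their true status. With prevalence π and q = π·Se + (1−π)(1−Sp):

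- apparent Se = [(1−u)π·Se + u·q] / [(1−u)π + u·q]
- apparent Sp = [(1−u)(1−π)·Sp + u(1−q)] / [(1−u)(1−π) + u(1−q)]

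For example, π = 0.5, Se = 0.70, Sp = 0.85 and u = 0.1 give q = 0.425 and apparent Se = (0.315 + 0.0425) / (0.45 + 0.0425) = 72.6%. Across π of 50% or 70%, and Se/Sp of 70%/85% or 80%/90%:

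| u | Rise in sensitivity (points) | Rise in specificity (points) |
|---|---|---|
| 0 | 0 | 0 |
| 10% | 1.7 to 2.6 | 1.1 to 2.2 |
| 20% | 3.5 to 5.3 | 2.2 to 4.2 |
| 30% | 5.3 to 8.0 | 3.2 to 6.0 |

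**Scale against sampling error.** In illustration 1 the 95% half-widths are 1.96 × √(0.8 × 0.2/160) = 6.2 points for sensitivity and 1.96 × √(0.9 × 0.1/80) = 6.6 points for specificity. The largest biases there, 4.1 and 4.7 points, are smaller. In illustration 2 the half-width for sensitivity runs from about 5.5 to 8.2 points, so at u = 30% the bias is of about the same size.

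**The case against.** - **The article nowhere says that the Ig/TCR or NGS result enters this study's diagnosis.** This stands. The Discussion sentences are cited background about the field, and only TCR rearrangement is called a criterion there; Ig rearrangement is described as a marker that can be used in diagnosis. A reader might infer that the study's diagnostic value is already inflated, or that agreement in the open cases will be complete by construction. The text supports neither: both follow only if the molecular result settles those cases, and the article neither says so nor rules it out.
- **This is a condensed article, and reading order and blinding may be in the full protocol.** This stands for the masking of gel and NGS readers, which is therefore not pressed here. It has less force for the reference diagnosis: the article gives that its own heading and defines it in a form that admits the test under study.
- **Sensitivity and specificity are not the article's terms; it speaks of association.** True, but the association is biased by the same mechanism, as the odds ratios show.
- **The size is assumed and modest.** This stands. In the first illustration the bias stays below sampling error. Sampling error shrinks with more data, however, and this bias does not.
- **Excluding molecular results from the reference leaves open cases without a truth.** This also stands, and limits what the fix can deliver.

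**Conclusion.** The concern holds in conditional form. Section 2.3.3 names a classification and does not make the reference diagnosis independent of the test under study, while the rest of the article treats gene analysis as part of diagnosis. If molecular results settle the cases that HE and immunohistochemistry leave open, the association between rearrangement and diagnosis is biased upward. The size is roughly 1 to 8 percentage points in sensitivity or specificity when 10% to 30% of cases are settled that way. That range rests wholly on assumed prevalence, accuracy and share of open cases, and on a correct reference in all other cases. A statement that the results are inflated would go beyond the document. The point still merits a change to the protocol, because the safeguard has to be in place when diagnoses are recorded.

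**What to change.** In section 2.3.3, state that:

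1. the research reference diagnosis is assigned under the named classification from HE, the listed immunohistochemistry and clinical data only;
2. it is recorded with a date stamp as lymphoma, not lymphoma or open before the BioMed-2 and NGS results are released, and the release date is recorded too;
3. the main comparison is reported with and without the open cases. Where they are included, the report says how they were classified and that this classification may not be independent of the test;
4. the open cases are described as their own stratum.

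The routine clinical report is unaffected and may use all results.

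The cost is one paragraph and two date fields in the database. Reported agreement may be somewhat lower. Accuracy cannot be estimated in the open stratum, which has no independent reference, and the result without open cases applies only to cases that morphology and immunohistochemistry can settle. If the full protocol does not already cover it, reading gels and NGS under coded numbers without the histology would be a useful addition, but it could need extra staff.

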### Data collection

2.4

#### HE and immunohistochemical detection

2.4.1

Paraffin embedded tissues will be sectioned with a thickness of 4 μm, and HE staining will be carried out by automatic HE staining apparatus. Immunohistochemical staining will be performed with DAKO Link48 automatic immunohistochemical staining apparatus. The selected immunohistochemical markers include CD20, CD3, CD79, CD5, CD4, CD8, TIA-1, GranzymeB, CD56, CD10, MUM1, Bcl-2, Bcl-6, CyclinD1, CD30, and CD15.

#### Deoxyribonucleic acid (DNA) extraction and rearrangement detection

2.4.2

Genomic Deoxyribonucleic acid (DNA) will be extracted from 240 paraffin embedding tissue samples. The IGH, Immunoglobulin kappa (IGK), LGL, T cell receptor gamma (TCRG), T cell receptor delta (TCRD), and T cell receptor beta (TCRB) rearrangement in genomic DNA will be analyzed using the European biomed-2 system. Additionally, the Next-generation sequencing (NGS) technology will be adopted for probing mutations. The detected mutations in lymphoma associated genes will be recorded, as well as the mutation ratio (the percentage of reads of this mutant site to the total number of reads that cover this site).

### Statistical plan

2.5

Excel will be used to establish the database, and SPSS 22.0 statistical software will be used for statistical analysis in this study.

### Dissemination

2.6

This study has been approved by the ethics committee of Deyang people's hospital. All participants immediate family members will sign the informed consent after being informed about the goals and methods of the study. The present study will be conducted in accordance with Declaration of Helsinki.

## Discussion

3

There are 2 categories of lymphoma: Hodgkin lymphomas and NHL.^[11,12]^ NHL can be driven by genetic and environmental risk factors.^[13]^ DLBCL is the most common adult lymphoid malignancies^[14,15]^ which is consistent with our analysis. It is known that DLBCL is more common in adults than in children, with a dramatic increase in incidence at 50 years old.^[16]^ Although some patients can be relieved after treatment, due to the non-specific molecular pathogenesis of DLBCL^[17]^ and its significant heterogeneity, some advanced-stage patients cannot be cured by standard immunochemotherapy.^[12]^ Therefore, early detection and treatment of DLBCL are still a challenging problem. To date, gene analysis combined with histopathology and immunophenotypic analysis can provide a new approach for the diagnosis of malignant tumors.^[18]^ Genomic rearrangement is an important oncogenic mechanism in human tumors,^[19]^ which may produce fusion transcripts encoding chimeric proteins with new functions.^[6]^ Many studies have shown that the IG gene rearrangement is a specific marker of B lymphocyte cloning^[19,20]^ and can be used in diagnosis of B cell lymphoma.^[21,22]^ The detection of IG gene rearrangement can help determine the nature of the lesion and distinguish between benign or malignant lymphocytes.^[23,24]^ Additionally, TCR rearrangement is another criterion for the diagnosis of lymphocyte disease.^[10,25]^ Based on the PCR of IG and TCR, it has been standardized in the suspicious lymph node hyperplasia.^[26,27]^ However, early PCR strategy always induce false negatives and false positives, and it is unable to accurately distinguish between monoclonal and polyclonal PCR products.^[28,29]^ When taking the advantages of standardized BioMed-2, the disadvantages of traditional PCR assay can be addressed,^[8,30]^ and this multiple detection showed a great clinical value for PCR based Ig/TCR cloning detection.^[31]^

In conclusion, standardization of BioMed-2 gene rearrangement detection system is a powerful tool of lymphoma diagnosis, IGH, IGK, Immunoglobulin lambda (IGL) and TCR gene rearrangement distributions are distinct in different subtypes of lymphoma.
